**Strategies to improve adherence to interventions {11c}**

All drugs will be masked for all blind partners and patients. People who prescribe the drugs and handle the patients are aware of the nature of the drugs. All patient sampling will be performed at specific times each day.

If one of the doses of the study’s drug is forgotten, the appropriate dose of that drug will be replaced in the next dose. The reason for forgetting or deleting the drugs is written to evaluate and reduce the amount of error.

**Relevant concomitant care permitted or prohibited during the trial {11d}**

The side effects of drugs will be severely examined daily and any possible treatment will be considered in advance. In some situations, and some patients, doctors may prescribe other drugs of dexamethasone family, such as methylprednisolone, with the equivalent dose. The standard regime for COVID-19, recommended by MOHME of Iran, may change in time during the study. Any changes in the medication regimen will be reviewed in a meeting with different clinicians and ways to use will be set up about further action.

**Provisions for post-trial care {30}**

The participants will be received the standard of care in all interventions and control arms during the study time and the days of follow up. The cases who suffer harm from trial participation, if any, will be received all kinds of free medical services.

**Outcomes {12}**

**Primary outcome**

An increase in the SpO2 level to reach more than 90% in each case, which will be assessed by the oximeter.

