**Abstract**

**Background:** The pandemic of Coronavirus Disease 2019 (COVID-19) affects the whole health system and the global economy. One of the reasons is that there is unfortunately little information about disease management especially in critically ill patients of COVID-19. A significant percentage of these patients develop acute respiratory distress syndrome (ARDS) due to cytokine storm. We hypothesize early administration of corticosteroids alone or in combination with intravenous immunoglobulin (IV-IG) and interferon-beta can improve the outcome of the disease.

**Methods:** This is a phase two multi-center randomized controlled trial (RCT) with three parallel arms (1:1:1). In each arm, 35 subjects will be enrolled. Each eligible subject will be allocated in an intervention group or control group with a simple randomization method. The control and two other groups will be received the standard treatment for COVID-19. The intervention 1 group will be also received dexamethasone, at the first 24 hours' time of admission, and will be continued base on the improvement of the level of SpO2. Another group will be received dexamethasone for the first three days. In the groups of 1 and 2 interventions, IV-IG and interferon-beta will be supported the treatment after 24 or 72 hours of dexamethasone prescription, respectively. The cases will be followed up for one month after discharge. The primary outcome will be an improvement in the level of SpO2 of more than 90%. The secondary outcomes will be the hospital length of stay, intubation status, and the percentage of patients who are free of mechanical ventilation, the mortality rate during hospitalization, and one month after the admission time.

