**Secondary outcomes**

The duration of hospital stays; intubation status and the percentage of patients who are free of mechanical ventilation; the mortality rates during hospitalization and one month after the admission time.

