**Participant timeline {13}**

All participants will be visited daily as long as they are hospitalized. If a person is discharged from the hospital earlier than 14 days, all his/her outcome factors will be monitored by phone or visiting at home. The secondary outcomes will be checked on day 14 in hospitalized patients or on the day of discharge. Each participant will be followed for one month. All interventions will be administrated to patients at a specific time each day. Monitoring and sampling, if needed, will be taken at the same time for a case in each day.

Figure 1: Flow chart of randomization and treatment assignment

[figure not shown]

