**Assignment of interventions: Blinding**

**Who will be blinded {17a}**

The PI is unblinded and is responsible for the study and will handle all team. However, this person will not play a role in examining the data and interpreting the results. An unblinded researcher (a pharmacist) will cover the drug’s bottles with aluminium foil and prepare them interventions and control drugs in a syringe with a code so that patients are blinded. This person will not be in contact with patients. The staff and nurses, caring for the patients, will be unblinded for each study group due to the nature of this study. The staff that take outcome measurements will be blinded. The laboratory technicians will also be blinded as well as the statistical team. These study statisticians will have access to coded data and will analyse the data labelled as group X, group Y, and group Z.

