**Data collection and management**

**Plans for assessment and collection of outcomes {18a}**

Several employees will daily complete all demographic and laboratory information of the patients and imported them to HIS. These persons are blinded about different study groups. The relevant patient data will be extracted via HIS and, if needed, will be completed by direct daily observation and review of patients' files by an unblinded person. The level of SpO2 (the primary outcome) will be daily measured by oximeter and the second outcomes will be extracted from HIS and evaluated. It will be assumed that all vital information of patients will be monitored continuously, as most data of patients in ICU are recorded as routine care.

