**Plans to promote participant retention and complete follow-up {18b}**

All related data about the outcomes including the daily level of SpO2, vital status, intubation status, the hospital stay length, and the time of discharge will be obtained during the hospitalization, day 14, and followed up one month after the discharge time. The data will be obtained by HIS, physical visit on a bed or a telephone interview. The main coordinator will provide written feedback and send an acknowledgment to the participants or their families. Besides, all cases who withdraw their study participation will be followed one month and If they need management and health services, they will be taken care of. Moreover, information from people who have dropped out of the study will also be checked if they have received enough doses of the drugs and will not be replaced by other patients.

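### The primary outcome fixes no assessment day, no oxygen condition and no rule for ventilation or death, so a patient who worsens and is ventilated can be scored a success

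*Protocol*

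**What the plan says.** Outcomes {12} gives the primary outcome in one sentence: "An increase in the SpO2 level to reach more than 90% in each case, which will be assessed by the oximeter". The Abstract adds nothing to it: "The primary outcome will be an improvement in the level of SpO2 of more than 90" per cent.

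On timing, Plans for assessment and collection of outcomes {18a} says "The level of SpO2 (the primary outcome) will be daily measured by oximeter". Section {18b} says that outcome data, daily SpO2 among them, "will be obtained during the hospitalization, day 14, and followed up one month after the discharge time". Participant timeline {13} sets day 14 or discharge for the secondary outcomes only. For patients discharged before day 14 it says "all his/her outcome factors will be monitored by phone or visiting at home".

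On respiratory failure, Eligibility criteria {10} excludes patients who need intubation, so ventilation can arise only after entry. It then appears as a secondary outcome: "intubation status and the percentage of patients who are free of mechanical ventilation". The SpO2 threshold in the case definition in {10} also carries no oxygen condition. Section {11b} withdraws some patients who worsen but keeps collecting their information, and {20c} analyses all outcomes by intention to treat.

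On blinding, {17a} says "The staff and nurses, caring for the patients, will be unblinded for each study group due to the nature of this study". The same section says that those who take outcome measurements are blinded.

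**The concern.** SpO2 depends on the support being given as well as on the state of the lungs. More oxygen, or a ventilator, can bring a reading above 90% in a patient whose disease is getting worse. A success rule with no oxygen condition, and with no failure status for ventilation or death, therefore cannot separate recovery from rescue.

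The primary and secondary outcomes can then point in opposite directions for the same patient. If one arm has more respiratory failure, its extra ventilated patients can be added to its primary successes, which can hide a difference or reverse its sign. Oxygen support is in the hands of carers who know the allocation, so its use could differ between arms for reasons unrelated to benefit.

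Without a deciding day, the analyst could also choose among any reading, the last reading or the day-14 reading after seeing the data, and these need not agree.

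**Working it through.** **The plan's own figure.** Sample size {14} gives 35 per group at two-sided 5% and 80% power, but no effect size in numbers, so 35 cannot be reproduced. Working backwards, 35 per group corresponds to a standardised difference of √2 × (1.960 + 0.842)/√35 = 0.67 or, for a success proportion, to about 40% against 73% (normal approximation, no continuity correction). The protocol does not say which, if either, was intended.

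**Tracing one patient through the text.** All steps use the protocol's own rules.

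1. The patient enters with SpO2 below 90% and no need for intubation ({10}).
2. The patient worsens, is intubated, and the daily oximeter reading rises above 90%.
3. Primary outcome {12}: the level has risen to above 90%, so the definition is met.
4. Secondary outcome: the patient is not free of mechanical ventilation, so this is a failure.
5. Section {11b} may withdraw the patient, but sets no failure status. Section {20c} keeps the patient in the analysis.

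No section breaks this chain.

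**Illustration 1: unequal intubation.** Assumed inputs: 14 of 35 intubated in arm A and 7 of 35 in arm B; all intubated patients read above 90%; a share p of the non-intubated succeed in both arms.

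- Arm A: (14 + 21p)/35
- Arm B: (7 + 28p)/35
- A minus B: (7 − 7p)/35 = 0.20(1 − p), that is 20(1 − p) points in favour of the arm with more intubation

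| p | Arm A | Arm B | A − B |
|---|---|---|---|
| 0.6 | 26.6/35 = 76% | 23.8/35 = 68% | +8 points |
| 0.8 | 30.8/35 = 88% | 29.4/35 = 84% | +4 points |
| 1.0 | 100% | 100% | 0 |

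If intubated patients are scored as failures instead, the rates are 21p/35 and 28p/35. At p = 0.6 these are 12.6/35 = 36% and 16.8/35 = 48%, a difference of 12 points the other way. The scoring rule alone changes the sign.

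**Illustration 2: a real benefit removed.** Assumed true recovery is 40% (control) against 60% (treated), and 50% against 20% of the non-recovered are ventilated to above 90%.

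- Control: 0.40 + 0.60 × 0.50 = 70%
- Treated: 0.60 + 0.40 × 0.20 = 68%

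A 20-point benefit is scored as a 2-point deficit.

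**Illustration 3: equal misclassification.** Assumed true recovery is 40% against 73%, with 25% of the non-recovered scored as successes in both arms.

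- Control: 0.40 + 0.60 × 0.25 = 55.0%
- Treated: 0.73 + 0.27 × 0.25 = 79.75%
- The difference falls from 33 to about 25 points.

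With power = Φ{[√n·Δ − 1.96√(2p̄(1 − p̄))]/√(p₁(1 − p₁) + p₂(1 − p₂))} and n = 35, power falls from 81% to 60%. Restoring 80% would take 56 per arm. Here the error costs power without reversing the result.

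**The case against.** The strongest reply is that the protocol is silent, and that scoring rules for intercurrent events are often left to an analysis plan, which is not at hand. The first half stands. A reader might infer that the protocol deliberately counts any reading, on any day and on any support. It does not say so; it only permits that scoring. The second half does not close the gap. The time of assessment and the conditions of measurement are part of what the primary outcome is, and the protocol sets a time for the secondary outcomes. An analysis plan also cannot restore oxygen device and flow if they were not recorded, and the data items named in {9} and {18b} do not include them.

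Four further inferences are tempting but not supported:

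- **The primary outcome is read unblinded.** Section {18a} lets gaps in the hospital-system data be completed from patients' "files by an unblinded person", but {17a} blinds those who take outcome measurements. Only the influence of unblinded carers on oxygen support is supported.
- **SpO2 is unobtainable after discharge.** A phone call cannot be relied on for it, but {13} also provides home visits.
- **Longer stays inevitably inflate success.** With a 5% or 10% daily chance of a transient reading above 90%, 14 readings give 1 − 0.95¹⁴ = 51% or 1 − 0.90¹⁴ = 77% with at least one. Those rates are assumed, the formula needs independent readings, which serial SpO2 in one patient is unlikely to give, and {13} continues monitoring after early discharge.
- **The trial cannot answer its efficacy question at all.** Intubation, freedom from ventilation and mortality are prespecified secondary outcomes, so an imbalance would be reported, though not in the primary result.

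**Conclusion.** The concern holds in this form: the sole primary outcome has no assessment day or window, no oxygen condition and no rule for ventilation or death, so a patient who is ventilated after worsening can be scored a success. This follows from the text and rests on no assumed figure.

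Its size does rest on assumptions, because the protocol gives no success or intubation rates. With 14 against 7 of 35 intubated and all of them above 90% on the ventilator, the worse arm gains 20(1 − p) points: 8 at p = 0.6 and none at p = 1. If fewer ventilated patients reach 90%, or intubation is balanced, the distortion is smaller. Since the direction of the primary result can change, the definition should be settled before any primary analysis.

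**What to change.** Amend Outcomes {12}, and the Abstract to match:

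- **Time.** Assess success at a fixed time, for example day 14 after randomisation, which fits the day-14 contact in {13} and {18b}.
- **Success.** Alive, not mechanically ventilated at any time up to that day, and SpO2 above 90% under a stated oxygen condition that is the same at baseline and at outcome.
- **Failure.** Any death or mechanical ventilation by that day, whatever the earlier or later readings.
- **Early discharge.** Use a home-visit reading or, failing that, the last in-hospital reading.
- **Assessors.** Readings are taken by the blinded outcome staff already named in {17a}.

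Requiring two consecutive readings above 90% would guard against transient values, but is optional.

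Costs: ethics and registry approval under {25}, and one extra recorded field (oxygen device and flow) with each reading. Trial status shows recruitment already under way, so oxygen data may be missing for patients already enrolled; how their readings are handled should be stated. The success rate will be lower than under the present wording, so {14} should restate the basis for 35 per arm, with explicit success rates, for the new definition.

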**Secondary outcomes**

The duration of hospital stays; intubation status and the percentage of patients who are free of mechanical ventilation; the mortality rates during hospitalization and one month after the admission time.

**Participant timeline {13}**

All participants will be visited daily as long as they are hospitalized. If a person is discharged from the hospital earlier than 14 days, all his/her outcome factors will be monitored by phone or visiting at home. The secondary outcomes will be checked on day 14 in hospitalized patients or on the day of discharge. Each participant will be followed for one month. All interventions will be administrated to patients at a specific time each day. Monitoring and sampling, if needed, will be taken at the same time for a case in each day.

Figure 1: Flow chart of randomization and treatment assignment

[figure not shown]

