**Statistical methods**

**Statistical methods for primary and secondary outcomes {20a}**

All statistical analysis will be done by SPSS Statistics version 16 or will be analysed by R software. At first, the normality of variables will be checked using a Kolmogorov-Smirnov test. The continuous data with normal or skewed distribution will be analysed and showed using the number (N), mean and standard deviation (SD), or median and inter-quartile range (IQR), respectively. The frequencies and percentages will be presented for the other type of data including categorical data.

The effect of outcomes between two interventions and the control groups will be assessed by chi-square or Fisher’s exact tests for the categorical data and the independent *t*-test will be used to evaluate the normal distribution data.

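### The secondary outcomes are timed by three conflicting clocks, and length of stay and ventilation-free status do not require the patient to be alive

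*Protocol*

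**What the plan says.** The protocol places the secondary outcomes in time in three ways.

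- **Day 14 or discharge.** Participant timeline {13}: "The secondary outcomes will be checked on day 14 in hospitalized patients or on the day of discharge". The sentence covers all secondary outcomes without exception. Just before it, the same section says that for a patient discharged before day 14, "all his/her outcome factors will be monitored by phone or visiting at home". It also promises one month of follow-up without naming the starting point.
- **One month after admission.** Secondary outcomes lists "the mortality rates during hospitalization and one month after the admission time", and the Abstract agrees: "the mortality rate during hospitalization, and one month after the admission time".
- **One month after discharge.** Abstract: "The cases will be followed up for one month after discharge". Plans to promote participant retention {18b} names "day 14, and followed up one month after the discharge time".

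Duration of stay, intubation status and the percentage free of mechanical ventilation are listed under Secondary outcomes with no time point and no requirement that the patient be alive. Section {20a} compares categorical data by chi-square or Fisher's exact test and normally distributed data by t-test. Section {20c} applies intention to treat to all outcomes. The limitations paragraph of the Discussion describes mortality in this population as inherently high.

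**The concern.** There are two linked problems.

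First, an outcome needs one origin and one horizon. Here a single sentence assigns all secondary outcomes to a check that does not fit several of them, while other sections use different clocks. Two analysts following different sections would produce different values for the same patient.

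Second, death ends a hospital stay and removes any later chance of intubation. If stay and ventilation-free status are computed as worded, with every randomised patient included, deaths pull both outcomes in the direction that looks good. An arm with more early deaths could then appear better on two of the secondary outcomes.

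**Working it through.** **1. The clocks side by side.** The protocol has no calculation to reproduce here, so the test is whether the stated times agree. Take a month as 30 days (assumption) and count from admission. The day-14/discharge check falls on min(stay, 14), a month after admission on day 30, and a month after discharge on stay + 30.

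| Stay (days) | Day-14/discharge check | One month after admission | One month after discharge |
|---|---|---|---|
| 5 | day 5 | day 30 | day 35 |
| 10 | day 10 | day 30 | day 40 |
| 14 | day 14 | day 30 | day 44 |
| 21 | day 14 | day 30 | day 51 |

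The check never falls later than day 14, so by itself it cannot supply mortality at day 30. For the 21-day stay it comes 7 days before discharge, so it cannot supply the length of that stay. For intubation and ventilation-free status it gives a reading time that runs from day 5 to day 14 across these patients and depends on another outcome.

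**2. Death as worded.** Consider a patient who dies on day 3 without having been intubated. Intention to treat keeps the patient in. Duration of stay is 3 days. The patient was never ventilated and so falls in the ventilation-free percentage. Nothing in the protocol alters either value.

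**3. Size for length of stay.** All inputs are assumptions: survivor stays are lognormal with median 11 days and log-SD 0.45, the same in both arms; time to death is lognormal with median 5.5 days and log-SD 0.45; mortality is 10% vs 30%.

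- Lognormal mean = median × exp(log-SD²/2), and exp(0.45²/2) = 1.1066.
- Survivors: 11 × 1.1066 = 12.17 days. Deaths: 5.5 × 1.1066 = 6.09 days.
- Mean stay at 10% mortality: 0.9 × 12.17 + 0.1 × 6.09 = 11.56 days.
- Mean stay at 30% mortality: 0.7 × 12.17 + 0.3 × 6.09 = 10.35 days.
- Difference: 0.20 × (12.17 − 6.09) = 1.2 days in favour of the arm with three times the deaths.

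The gap is proportional to the mortality difference: about 0.6 days for a 10-point difference and 1.8 days for 30 points. In this example 27% and 21% of stays pass day 14. If stays really were cut there, simulated means are 10.2 vs 9.3 days, a gap of 0.9.

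With 35 per arm, simulation gives a t-test result significant in the wrong direction in about 14% of trials (19% with the cut).

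A second set of assumptions (survivors average 12 days, deaths average 5 days, mortality 20% vs 40%) gives 0.8 × 12 + 0.2 × 5 = 10.6 against 0.6 × 12 + 0.4 × 5 = 9.2 days, a gap of 1.4.

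**4. Size for ventilation.** Assume 30% vs 25% intubated, and 10% vs 20% dying without intubation. Never ventilated: 70% vs 75%, favouring the second arm. Alive and never ventilated: 70 − 10 = 60% vs 75 − 20 = 55%, favouring the first. The direction reverses.

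**The case against.** **The protocol does not declare early death a good result.** A reader might infer that it does. It is silent on how deaths enter these two outcomes, it reports mortality separately, and a SAP that is not shown may contain a rule. This stands as far as it goes: the wrong-direction risk is conditional on the wording being applied as it is. It does not remove the point, because the definitions are stated in the protocol without a condition of being alive and all patients are retained.

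**Mortality is not distorted in this way.** A reader might also infer that the conflicting clocks make mortality windows differ between arms. They do not for the one-month outcome: admission is its stated origin in both places, and follow-up to a month after discharge always reaches that date, since discharge cannot precede admission. In-hospital mortality does depend on time in hospital, but by definition.

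**Day 14 need not be a cut-off.** The protocol says outcomes are checked then, not that collection stops. Patients are visited daily while in hospital, section {18b} gathers vital status, intubation, stay length and discharge time during hospitalisation and at follow-up, and section {18a} takes the secondary outcomes from the hospital information system. So it would be wrong to say that later deaths, intubations or days are lost. What remains is that the sentence fixing the assessment time contradicts that collection plan.

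**The figures are assumed.** True. They show direction and rough scale only, and even in the main example most trials of this size would not reach significance on length of stay.

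**Normality testing.** Section {20a} states that "the normality of variables will be checked using a Kolmogorov-Smirnov test" and names no comparison test for skewed data. That is a side issue which a SAP would ordinarily settle, and this point does not rest on it.

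**Conclusion.** The point holds in two parts. The contradiction in assessment times is in the current text and needs no assumption beyond reading the sections together. The death problem follows from the outcomes as worded, combined with intention to treat and a population described as having high mortality. It affects length of stay and ventilation-free status only.

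The illustrated size is about 1.2 days of apparent benefit under the main assumptions, roughly 0.6 to 1.8 days as the mortality difference runs from 10 to 30 points, and a possible reversal for ventilation. No rate or stay in these examples comes from the documents. The outcomes concerned are secondary, so this should be corrected, but it does not touch the primary comparison.

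**What to change.** - Replace the day-14/discharge sentence in Participant timeline {13} with one origin and a fixed one-month horizon for the secondary outcomes. The admission origin under Secondary outcomes may stay. Name that origin for the one-month follow-up, and align the Abstract and section {18b} with it.
- Report ventilation as alive and free of mechanical ventilation at one month.
- Analyse length of stay so that death is not a short stay. Two workable options are time to discharge alive with death as a competing event, or days alive and out of hospital to day 30 with death scored 0, compared by a rank test. Choose one before outcomes are compared by arm.

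Cost: a protocol amendment through the registry and the ethics committee, as section {25} requires for changes to outcomes and analyses, in a trial already recruiting; and slightly more analysis work. No new data are needed, because hospital records and one-month contact are already planned.
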